## Abstract

**Background:**

Elbow dislocations can be classified as simple or complex. Simple dislocations are characterized by the absence of fractures, while complex dislocations are associated with fractures. After reduction of a simple dislocation, treatment options include immobilization in a static plaster for different periods of time or so-called functional treatment. Functional treatment is characterized by early active motion within the limits of pain with or without the use of a sling or hinged brace. Theoretically, functional treatment should prevent stiffness without introducing increased joint instability. The primary aim of this randomized controlled trial is to compare early functional treatment versus plaster immobilization following simple dislocations of the elbow.

**Methods/Design:**

The design of the study will be a multicenter randomized controlled trial of 100 patients who have sustained a simple elbow dislocation. After reduction of the dislocation, patients are randomized between a pressure bandage for 5-7 days and early functional treatment or a plaster in 90 degrees flexion, neutral position for pro-supination for a period of three weeks. In the functional group, treatment is started with early active motion within the limits of pain. Function, pain, and radiographic recovery will be evaluated at regular intervals over the subsequent 12 months. The primary outcome measure is the *Quick *Disabilities of the Arm, Shoulder, and Hand score. The secondary outcome measures are the Mayo Elbow Performance Index, Oxford elbow score, pain level at both sides, range of motion of the elbow joint at both sides, rate of secondary interventions and complication rates in both groups (secondary dislocation, instability, relaxation), health-related quality of life (Short-Form 36 and EuroQol-5D), radiographic appearance of the elbow joint (degenerative changes and heterotopic ossifications), costs, and cost-effectiveness.

**Discussion:**

The successful completion of this trial will provide evidence on the effectiveness of a functional treatment for the management of simple elbow dislocations.

**Trial Registration:**

The trial is registered at the Netherlands Trial Register (NTR2025).

## Background

The elbow joint is the second most commonly dislocated joint in adults. The annual incidence of elbow dislocations in children and adults is 6.1 per 100,000 [1]. Elbow dislocations are classified as simple or complex [2]. Simple dislocations are dislocations without fractures. Complex dislocations are associated with (avulsion) fractures of the distal humerus, radial head, ulna, or coronoid process. Conn et al. observed 414 injuries of the elbow, which included 58 elbow dislocations in both children and adults [3]. In 51% of these patients, the dislocations were of the simple type. Josefsson et al. observed 24 simple elbow dislocations in 52 patients (46%) who were 16 years old and older [4].

Elbow dislocations can also be classified by the direction of their displacement, i.e., posterior or anterior. Posterior dislocations can be subdivided into medial and lateral dislocations. Anterior dislocations are very rare. In the study by Conn et al., 96% of the dislocations were of the posterior or lateral type [3]. Moreover, Josefsson et al. observed no anterior dislocations in 52 elbow dislocations [4].

Different treatment modalities can be applied following reduction, including plaster immobilization, surgical treatment of ruptured collateral ligaments, functional treatment, or combinations. There is little available literature about treatment of elbow dislocations. One randomized controlled trial (RCT) was identified in which suture repair of the collateral ligaments was compared with conservative treatment with plaster [5]. No differences were found for loss of extension and flexion after more than one year, although a trend was found for enhanced flexion at five and ten weeks for the plaster group. However, this study lacked power, with a sample size of only 14 patients in each arm. When comparing functional treatment versus plaster immobilization, only one RCT was retrieved from the literature [6]. Extension and flexion of the elbow did not differ between the groups after one year. Nevertheless, a difference in elbow extension was observed at three months, favoring the patients treated functionally. Furthermore, when two observational studies were pooled comparing functional treatment with plaster immobilization, functional treatment showed a statistically significant better result for pain and range of motion (ROM) [7,8].

Three observational studies comparing different periods of plaster immobilization after reduction showed a larger ROM after shorter immobilization, but this finding was statistically significant in only one study [9-11]. Moreover, these studies may be confounded by the severity of the injury, as worse cases were probably immobilized longer.

An important question following reduction of simple elbow dislocations is whether or not the elbow is stable. Signs of instability are redislocation, a positive pivot shift test, positive valgus and varus stress testing, and radiographic incongruence. In the studies described above, stability testing was either not performed, or the tests differed between the studies. In these eight studies, only one recurrent dislocation after plaster treatment was mentioned [7] (i.e., one recurrence in 342 patients (0.3%)), and signs of gross instability were not mentioned. Therefore, we conclude that the majority of the patients included in these studies had simple dislocations, which remained stable after reduction. For this type of dislocation, literature suggests that plaster immobilization for more than two weeks following reduction may lead to limited ROM [12,13]. Therefore some authors state that early functional treatment should be the treatment of choice. Functional treatment is defined as early active movements within the limits of pain with or without the use of a sling or a hinged brace [6-8].

A recent electronic survey of 90 trauma surgeons in the Netherlands revealed that 60% of the patients with a simple elbow dislocation were generally treated with plaster immobilization for three weeks or longer [14].

The primary objective of this study is to compare the *Quick-*DASH (Disabilities of the Arm, Shoulder, and Hand) questionnaire scores after functional treatment versus plaster immobilization in adult patients who sustained a simple elbow dislocation. Secondary aims are to examine the effect of functional treatment versus plaster immobilization on functional outcome (Mayo Elbow Performance Index (MEPI) and Oxford elbow score), the level of pain (Visual Analog Scale (VAS)), ROM, the rate of secondary interventions and complications, health-related quality of life (Short Form-36 (SF-36) and EuroQol-5D (EQ-5D)), costs, and cost-effectiveness in these patients.

## Methods/Design

### Study design

The FuncSiE trial will follow a multicenter, randomized controlled trial design. Twenty-five centers in the Netherlands will participate. The study started August 26, 2009.

### Recruitment and consent

Eligible patients presenting to the emergency department (ED) with a simple elbow dislocation will be informed about the trial at the ED after reduction of the dislocated elbow. They will receive written information and a consent form from the attending physician, the clinical investigator or a research assistant. After providing informed consent, eligible patients will be randomized within one week. Participants will be allocated to one of two treatment arms using a web-based randomization program that will be available 24 hours a day. Variable block randomization will be accomplished via a trial website. Allocation will be at random.

It is not possible to blind surgeons and patients for the allocated treatment. In order to reduce bias, an independent researcher without knowledge of the prescribed treatment will perform follow-up measurements. In addition, radiographs will be blinded and evaluated in duplicate, and analysis will be done in a blinded fashion.

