### Intervention

Reduction can be performed under general, regional, or local anesthesia or without anesthesia, depending upon the preference of the surgeon. The method of choice will be recorded, but not standardized.

Following reduction, the affected arm will be put in either a pressure bandage (e.g., Tubigrip^®^) or a plaster of Paris for three weeks. Both treatment groups will be advised to use a sling; 5-7 days for the functional group, and up to three weeks in the plaster group.

In the functional group, early active movements within the limits of pain are allowed. Patients will be free to select their own physical therapist. Physical therapy is commenced after two days according to a predefined protocol. Patients will be asked to hand over to their physical therapist the following instructions. Exercises will be performed in a supine overhead position with the shoulder flexed at 90°. When coming into the overhead position, the shoulder is held in adduction and neutral to external rotation. The arm is not allowed to cross the midline. This position is controlled by holding the wrist with the healthy hand. In the supine position, with the shoulder in 90° of forward flexion and the forearm maintained in pronation (with the forearm resting on the forehead), gentle active assisted supination and pronation is performed. The second exercise is performed in the same position. The shoulder is placed in 90° of forward flexion and the elbow in 90° or more flexion. The forearm is held in full pronation. Gentle active and active assisted elbow flexion to full range and elbow extension are performed as tolerated and are not to exceed 30°. After three weeks, the sling will be removed, and the supine exercises will be replaced by active and active assisted elbow and forearm motions in the sitting or standing positions.

The plaster group is immobilized for three weeks and after removal of the plaster physical therapy is initiated according to the same protocol as described above.

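### The functional arm is given two incompatible sling durations (5 to 7 days, and three weeks); secondarily, allocation up to a week after consent can delay the early motion under test

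*Protocol article*

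**What the plan says.** All references are to the protocol article.

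**Sling.** Under Intervention, both groups are advised to use a sling: "5-7 days for the functional group, and up to three weeks in the plaster group". The next paragraph concerns the functional group and opens with "In the functional group, early active movements within the limits of pain are allowed". It introduces a therapist sheet: "Patients will be asked to hand over to their physical therapist the following instructions". After describing the supine exercises, it ends with "After three weeks, the sling will be removed", at which point sitting or standing exercises take over. For the plaster group, "after removal of the plaster physical therapy is initiated according to the same protocol as described above".

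**Timing.** Under Recruitment and consent, patients are told about the trial in the emergency department after reduction, and "After providing informed consent, eligible patients will be randomized within one week". The web randomisation program runs around the clock. Under Intervention, "Following reduction, the affected arm will be put in either a pressure bandage" or a plaster, and for the functional group "Physical therapy is commenced after two days according to a predefined protocol". The text does not say whether the two days run from reduction or from allocation.

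**The concern.** The sling instruction is part of how the functional treatment is delivered, and the article fixes it at two values for the same arm. The conflict would be felt in practice. The trial runs in 25 centres, patients choose their own therapist, and they carry the instructions themselves. A therapist who follows the sheet would keep the patient in a sling for three weeks, while the hospital has advised about one. Days of sling use are recorded, but the record cannot show who complied when the plan does not say which duration is correct.

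The second issue is the start of motion. Early movement is the treatment being tested, and a patient does not belong to the functional group until allocated. A randomisation window of up to a week after consent overlaps the days in which that movement is meant to begin.

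**Working it through.** The plan gives no calculation on this point, so the check sets its statements side by side and counts days.

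**Sling duration, functional arm**

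Inputs, all from Intervention: advice to patients 5 to 7 days; therapist sheet three weeks = 21 days; plaster arm at most three weeks = 21 days.

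- Discrepancy: 21 − 7 = 14 days to 21 − 5 = 16 days.
- Ratio: 21/7 = 3.0 to 21/5 = 4.2.
- On the three-week reading, functional arm versus plaster maximum: 21 − 21 = 0 days' difference.

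Could the three-week sentence have been meant for the plaster arm, which uses the same exercise sheet? Those patients begin the exercises only once the plaster comes off, on day 21.

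- If the sentence counts from the start of their therapy, the sling would come off on day 21 + 21 = 42, against a stated maximum of 21.
- If it counts from reduction, they would skip the supine phase altogether.

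Neither reading removes the conflict.

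**Timing of allocated motion**

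Inputs: randomisation up to 7 days after consent (Recruitment and consent); functional-arm therapy after 2 days, origin not stated (Intervention). Assumption: consent on the day of reduction, day 0. Let d be the day of allocation, from 0 to 7.

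- Two days counted from reduction: earliest supervised therapy = max(2, d).
- Two days counted from allocation: earliest supervised therapy = d + 2.

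| Allocation day d | From reduction | From allocation |
|---|---|---|
| 0 | 2 | 2 |
| 2 | 2 | 4 |
| 3 | 3 | 5 |
| 5 | 5 | 7 |
| 7 | 7 | 9 |

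Patients allocated by day 2 fit on either clock. After day 2, a reduction clock is overrun by d − 2 days, at most 7 − 2 = 5. An allocation clock is never overrun, but supervised therapy moves to as late as day 9. Unsupervised active movement is not tied to day 2. As an allocated treatment, however, it cannot begin before allocation, so day 7 at the latest under the same assumption.

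**The case against.** **The sling is minor.** The Background defines functional treatment with the sling as optional, sling use is only advised, and the exercises start whether or not it is worn. This stands: the conflict does not change what the two arms are. It remains a contradiction in an instruction to be followed, and one that recording sling days cannot resolve.

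**The timing is not a contradiction.** The durations most naturally describe allocated treatments and so run from allocation, in which case nothing clashes. One week is a ceiling, randomisation is available at all hours, and a window gives patients time to decide. What is worn before allocation may be set out in the full protocol. Even day 9 falls short of the two weeks of immobilisation beyond which the Background expects loss of motion. Most of this stands, and it is why timing is the secondary point. What remains is that a compliant patient may start the motion under test about a week later than the text suggests.

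**Stronger readings that the document does not support**

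- A reader might infer that allocation can fall after the whole 5 to 7 day bandage period. With consent on day 0, the latest allocation is day 7, which is the end of that period. Going beyond it needs consent on day 1 or later. The text does not bar that, but does not describe it either.
- A reader might infer bias between arms. The delay to allocation arises before the arm is known, so it cannot differ systematically by arm.
- A reader might infer that late allocation disturbs the primary outcome through the visit schedule. Study procedures counts visits from the start of treatment, and the earliest Quick-DASH is at 4 weeks. Even if visits ran from reduction, that is 28 − 7 = 21 days after an allocation on day 7.

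**Conclusion.** The sling statement is wrong as written. The functional arm has two durations, 14 to 16 days apart, and the longer one matches the plaster arm's maximum. This rests on the wording alone and needs no assumption.

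The timing point holds in a limited form. Assuming consent on the day of reduction, compliant allocation can come up to 5 days after a therapy start counted from reduction, or supervised therapy can begin as late as day 9 if counted from allocation. Day 9 is the permitted extreme and not the expected delay. The consequence is possible dilution of the early-motion contrast, without bias between arms. The article gives no distribution of delays, so no effect on the Quick-DASH can be calculated.

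**What to change.** **Main change.** Correct the therapist instructions so that the functional arm has a single sling duration. The natural choice is 5 to 7 days, with only the exercise position changing at three weeks, unless the clinical investigators intend otherwise. This costs one line on the instruction sheet and the matching protocol wording. Inclusion has already begun, so the corrected sheet should go to the centres promptly.

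**Secondary change.** Randomise at consent where feasible, using the existing web program, and record the time from reduction to randomisation. This costs a line of protocol wording, one date field and a small logistic burden in the emergency department. Patients who want time to consider will still consent and start later, so late starts would be fewer and documented, but not abolished.

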### Study population

All persons aged 18 years or older presenting with a simple elbow dislocation at the Emergency Departments of the participating clinics are eligible for inclusion.

Patients meeting the following inclusion criteria are eligible for enrolment:

1. Adult men or women aged 18 years and older (with no upper age limit)

2. A simple dislocation of the elbow (i.e., without associated fracture) that can be reduced by closed means. Presence of a dislocation and absence of fracture(s) will be confirmed by a plain X-ray

3. Provision of informed consent by patient

If any of the following criteria applies, patients will be excluded:

1. Polytraumatized patients

2. Patients with complex, pathological, recurrent or open dislocations

3. Additional traumatic injuries of the affected arm

4. Patients undergoing surgical repair of collateral ligaments of the dislocated elbow joint

5. Patients with an impaired elbow function (i.e., stiff or painful elbow or neurological disorder of the upper limb) prior to the injury

6. Retained hardware around the affected elbow

7. History of operations or fractures involving the elbow

8. Patients with rheumatoid arthritis

9. Likely problems, in the judgment of the investigators, with maintaining follow-up (e.g., patients with no fixed address)

10. Insufficient comprehension of the Dutch language to understand a rehabilitation program and other treatment information, which will be judged by the attending physician

Exclusion of a patient because of enrolment in another ongoing drug or surgical intervention trial will be left to the discretion of the attending surgeon on a case-by-case basis.

### Intervention

Reduction can be performed under general, regional, or local anesthesia or without anesthesia, depending upon the preference of the surgeon. The method of choice will be recorded, but not standardized.

Following reduction, the affected arm will be put in either a pressure bandage (e.g., Tubigrip^®^) or a plaster of Paris for three weeks. Both treatment groups will be advised to use a sling; 5-7 days for the functional group, and up to three weeks in the plaster group.

In the functional group, early active movements within the limits of pain are allowed. Patients will be free to select their own physical therapist. Physical therapy is commenced after two days according to a predefined protocol. Patients will be asked to hand over to their physical therapist the following instructions. Exercises will be performed in a supine overhead position with the shoulder flexed at 90°. When coming into the overhead position, the shoulder is held in adduction and neutral to external rotation. The arm is not allowed to cross the midline. This position is controlled by holding the wrist with the healthy hand. In the supine position, with the shoulder in 90° of forward flexion and the forearm maintained in pronation (with the forearm resting on the forehead), gentle active assisted supination and pronation is performed. The second exercise is performed in the same position. The shoulder is placed in 90° of forward flexion and the elbow in 90° or more flexion. The forearm is held in full pronation. Gentle active and active assisted elbow flexion to full range and elbow extension are performed as tolerated and are not to exceed 30°. After three weeks, the sling will be removed, and the supine exercises will be replaced by active and active assisted elbow and forearm motions in the sitting or standing positions.

The plaster group is immobilized for three weeks and after removal of the plaster physical therapy is initiated according to the same protocol as described above.

### Outcome measures

The primary outcome measure is the *Quick-*DASH (Disabilities of the Arm, Shoulder and Hand) score, which reflects both function and pain [15]. The DASH Outcome Measure is a validated 30-item, self-reported questionnaire designed to help describe the disability experienced by people with upper-limb disorders and also to monitor changes in symptoms and function over time [15,16].

The *Quick-*DASH is a shortened version of the DASH Outcome Measure. Instead of 30 items, the Quick-DASH uses 11 items (scored 1-5) to measure physical function and symptoms in people with any or multiple musculoskeletal disorders of the upper limb. The right and left elbow will be assessed separately. At least 10 of the 11 items must be completed for a score to be calculated. The scores will be transformed to a 0-100 scale for easy comparison. A higher score indicates greater disability.

Like the DASH, the *Quick-*DASH contains 2 optional modules to measure symptoms and function in athletes, performing artists and other workers whose jobs require a high degree of physical performance. These optional models are scored separately; each contains four items, scored 1-5. All items must be completed for a score to be calculated.

The secondary outcome measures are:

• Functional outcome (Mayo Elbow Performance Index and Oxford Elbow Score)

• Pain level at both sides (VAS)

• Range of Motion of the elbow joint at both sides

• Rate of secondary interventions

• Rate of complications (secondary dislocation, instability, relaxation)

• Health-related quality of life: SF-36 and EQ-5D

• Radiographic appearance of elbow joint (degenerative changes and heterotopic ossifications)

• Cost

• Cost-effectiveness

The MEPI index is one of the most commonly used physician-based elbow rating systems. This index consists of five parts: pain (with a maximum score of 45 points), ulnohumeral motion (20 points), stability (ten points), the ability to perform five functional tasks (5 × 5 points) and the patient response. If the total score is between 90 and 100 points, it is considered excellent; between 75 and 89 points, good; between 60 and 74 points, fair; and less than 60 points, poor [17].

The Oxford elbow score is a 12-item questionnaire. It is comprised of three one-dimensional domains: elbow function, pain and social-psychological, with each domain comprising 4 items with good measurement properties [18]. This is a validated questionnaire in the UK and was translated to Dutch by the proper translation procedure, which uses the technique of translation and back-translation [19]. Permission for translation and the use of the OES for this study was obtained from Oxford and Isis Outcomes, part of Isis Innovation Limited (website: http://www.isis-innovation.com/)

Pain level will be determined using a 10-point Visual Analog Scale (VAS), in which zero implies no pain and ten implies the worst possible pain.

ROM will be measured on both sides using a goniometer.

Secondary interventions within one year of initial treatment to relieve pain or improve function will be recorded. This includes secondary revision of collateral ligaments and external fixator placement.

Complications within one year of initial treatment will be recorded. These include redislocation, pressure necrosis (plaster group only), post-traumatic dystrophy, and neurologic deficit.

The Short-Form 36 (SF-36) is a validated multi-purpose, short-form health survey with 36 questions that represent eight health domains that are combined into a physical and a mental component scale [20]. The Physical Component Scale (PCS) combines the health domains of physical functioning (PF; ten items), role limitations due to physical health (RP; four items), bodily pain (BP; two items), and general health perceptions (GH; five items). The Mental Component Scale (MCS) combines the health domains of vitality, energy, or fatigue (VT; four items), social functioning (SF; two items), role limitations due to emotional problems (RE; three items), and general mental health (MH; five items). Scores ranging from zero to 100 points are derived for each domain, with lower scores indicating poorer function. These scores will be converted to a norm-based score and compared with the norms for the general population of the United States (1998), in which each scale was scored to have the same average (50 points) and the same standard deviation (ten points).

The EuroQol-5D is a validated questionnaire for health-related quality of life [21,22].

Radiographic appearance (anteroposterior and lateral X-ray at one year): heterotopic ossification will be classified according the classification scheme of Broberg and Morrey as a bone exostosis or as a soft tissue ossification of a ligament, capsule or muscle ("myositis ossificans") [23]; degenerative changes will be classified as grade zero (no change), grade 1 (slight narrowing of the joint space with small osteophytes), grade 2 (moderate narrowing of the joint space, osteophytes and subchondral sclerosis), and grade 3 (severe narrowing of the joint space, large osteophytes, subchondral sclerosis and cystic deformation).

The incremental cost-effectiveness ratio of functional versus plaster treatment will be expressed in a cost-utility ratio, i.e., in terms of cost per QALY. The economic evaluation will be performed from a societal perspective, and will include both health care costs and costs of production losses. Health care costs will include costs of general practice care, medical specialist care, physical therapy, hospitalization, medication, and other costs directly associated with diagnosis, treatment and rehabilitation. Patients will be asked to administer a custom-made questionnaire to register their health care needs and production loss.

In addition to the outcome variables mentioned above, the following data will be collected:

a) Intrinsic variables (baseline data): age, gender, American Society of Anesthesiologists' ASA classification, tobacco consumption, alcohol consumption, comorbidity, social status/household composition, dominant side, and medication use.

b) Injury related variables: affected side, mechanism of injury, and assessment of varus, valgus and posterolateral rotatory instability.

c) Intervention-related variables: reduction delay (i.e., time between dislocation and reduction), time between injury and start of physical therapy, days of sling use, and number of physical therapy sessions

